## Introduction

### Background and rationale {6a}

Acute pancreatitis (AP) is a seriousthreat to human health globally. It is the third most common gastrointestinal, liver, and pancreatic principal diagnoses from hospital admissions in USA. Over 275,000 patients were admitted because of AP every year, with over 2000 deaths and 2,600,000,000 dollars spent [1–3]. The diagnosis of AP requires 2 of the following features: characteristic abdominal pain, biochemical evidence of pancreatitis, radiographic evidence of pancreatitis. AP can be categorized as mild, moderately severe, or severe based on the revised Atlanta classification [4]. Severe acute pancreatitis (SAP), defined as pancreatitis with persist organ failure (over 48 h), develops in 20–30% of AP patients, with high mortality (15%) [5, 6].

Gastrointestinal dysmotility is a common complication for AP patients, often resulting in abdominal distension, nausea, and vomiting. Delayed feeding and oral feeding intolerance (OFI) may also be associated with gastrointestinal dysmotility. Severe gastrointestinal dysmotility is associated with paralytic ileus and abdominal compartment syndrome (ACS), which can be lethal for SAP patients [7–9]. Currently, there is limited evidence for treating gastrointestinal dysmotility in AP patients.

Early enteral nutrition (EN) plays an important role in the management of AP by protecting the mucosal barrier and reducing bacterial translocation. Delayed feeding (generally defined as over 24 h after onset) is associated with higher rates of infected peripancreatic necrosis, multiple organ failure, and total necrotizing pancreatitis [10–14]. OFI is a well-known complication of AP and the burden can be high. OFI develops in nearly one in six patients with AP, leading to longer length of hospitalization and reduced quality of life [15–19]. ACS, defined by the increased intra-abdominal pressure > 20 mmHg in association with failure of at least one organ system, developed in 12% to 56% of patients and the mortality of SAP patients with ACS is around 24 to 75% [20–24].

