### Objectives {7}

The objective of this study is to investigate the efficacy and safety of neostigmine on treating SAP and to evaluate whether it can promote the recovery of intestinal function, making spontaneous defection and EN usage earlier, decrease intra-abdominal pressure, reduce mortality, organ failure and shorten hospital stay.

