#### Secondary outcome

Mortality of patientsNew-onset organ failure, defined as organ failure after randomization (not present at any time before randomization). Including respiratory failure (PaO_2_/FiO_2_ ≦ 300, or requirement of mechanical ventilation), circulatory failure (systolic blood pressure < 90 mmHg, despite adequate fluid resuscitation, or requirement for inotropic catecholamine support) and renal failure (creatinine level > 177 μmol/L after rehydration or new need for hemofiltration or hemodialysisIntra-abdominal pressure, measured indirect using bladder pressure [37] every day after enrollmentTiming of EN, defined as time from randomization to the initiation of tolerated ENBorborygmus, measured every day by member of study teamOccurrence of abdominal infection, based on the diagnosis when dischargingThe proportion of adverse events and serious adverse events identified in both groupsHealth economics, including length of ICU stay, length of hospital study, and total cost in hospital, documented based on hospital information system

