#### Sample size {14}

This is a randomized controlled trial. The bilateral significance level is 5% with an assurance of 90%. We estimate the standard deviation is 36 h, and the mean difference is 36 h. In the case of 1:1 ratio between intervention group and control group, a total of 44 patients will be needed (22 patients in each group). Considering a 20% drop-out rate, 56 patients will be recruited.

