### Statistical methods

#### Statistical methods for primary and secondary outcomes {20a}

Intention-to-treat (ITT): Nno one was excluded from the main analysis set after randomizationPer-protocol set (PPS): good compliance case data that meets the main inclusion and exclusion criteria and reach the primary endpoint

The number of participants selected and complete the study will be listed and the two analysis data sets (ITT and PPS) as specified above will be identified. Cases of protocol violation will also be listed with reasons documented. In terms of outcome indicator analysis, continuous variable indicators will count the number of cases (*n*), mean (*x*), standard deviation (SMD), median (*M*), minimum (min), and maximum (max). The difference between groups will be analyzed using Student’s *t*-test. Counting and grading data will be used to calculate the frequency and composition ratio. The *χ*
^2^ test/chi-square test will be used for differences between groups. Unless otherwise stated, all statistical tests will be conducted in a bilateral manner. All data will be entered in Microsoft Excel, and all statistical analyses will be performed using the SPSS version 25 statistical package.

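### ICU stay, hospital stay and time to tolerated enteral nutrition go to a t-test with no rule for death, so the comparisons can mislead if mortality or its timing differs between arms

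*Protocol article*

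**What the plan says.** Under Secondary outcome, the protocol article lists mortality, the timing of EN and a health-economics group made up of "length of ICU stay, length of hospital study, and total cost in hospital" (the second item is evidently hospital stay). EN timing runs from randomization to the start of EN that the patient tolerates, so it exists only for patients who get that far.

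The analysis section ({20a}) gives one rule for continuous variables: "The difference between groups will be analyzed using Student’s *t*-test". Item {20c} says that missing values will not be imputed. Item {20b} plans no subgroup or adjusted analyses. Under Recruitment {15}, follow-up stops when the patient leaves hospital. The article gives no censoring, competing-event, worst-rank or survivors-only rule.

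The Objectives section gives stay a clinical meaning: the drug is to "reduce mortality, organ failure and shorten hospital stay". The Background says of severe acute pancreatitis (SAP) that it "develops in 20–30% of AP patients, with high mortality (15"%), so deaths are to be expected.

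**The concern.** Two mechanisms are at work.

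- **Stay.** A hospital or ICU stay ends at discharge or at death. In a comparison of means, a death in the first week looks like a short stay, which is the favourable end of the scale if shorter is read as better. The same sentence of the Objectives hopes to lower mortality. If the drug succeeds there, patients who would have had short fatal stays have longer survivor stays instead, and the stay result moves the wrong way.
- **EN timing.** A patient who dies before tolerated EN has no value. With a t-test and no imputation, that patient cannot enter the comparison. What remains is a group selected after randomization, although the stated main analysis is by intention to treat.

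At stake is the reading of secondary outcomes that carry aims 3 and 4 of the Abstract. The primary outcome analysis and the sample size do not depend on this point.

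**Working it through.** **The plan's own figure.** Inputs from Sample size {14}:

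- Error rates, read as two-sided 5% and 90% power: "The bilateral significance level is 5% with an assurance of 90".
- Assumed spread and effect for the primary outcome: "We estimate the standard deviation is 36 h, and the mean difference is 36 h".
- Evaluable number, the first figure to reproduce: "a total of 44 patients will be needed (22 patients in each group".
- Allowance for losses, the second figure to reproduce: "Considering a 20% drop-out rate, 56 patients will be recruited".

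The check:

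- Per arm: 2 × (1.960 + 1.282)² × (36/36)² = 21.01, rounded up to 22, so 44 in total.
- With drop-out: 22 / (1 − 0.20) = 27.5, rounded up to 28 per arm, so 56 in total.

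The stated 44 and 56 reproduce. They concern the primary outcome only.

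**Expected deaths.** At the Background's 15%:

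- 56 × 0.15 = 8.4 deaths, or 28 × 0.15 = 4.2 per arm.
- The binomial chance of at least 4 deaths among 56 is 98%.

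**Mean stay.** Let m be mortality in an arm, S the mean stay of survivors and D the mean stay of patients who die. The mean for the arm is (1 − m) × S + m × D. If S and D are the same in both arms, the difference (neostigmine minus control) is

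(m_neo − m_ctrl) × (D − S).

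It is zero when mortality is equal, and its sign turns on whether D is below or above S. The documents give neither S nor D, nor mortality by arm, so every value below except the 15% is an assumption.

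| S (days) | D (days) | Mortality, control v neostigmine | Mean stay, control v neostigmine | Difference |
|---|---|---|---|---|
| 20 | 6 | 15% v 30% | 17.9 v 15.8 | −2.1 |
| 20 | 6 | 15% v 5% | 17.9 v 19.3 | +1.4 |
| 20 | 7 | 20% v 10% | 17.4 v 18.7 | +1.3 |
| 25 | 7 | 20% v 10% | 21.4 v 23.2 | +1.8 |
| 30 | 10 | 20% v 10% | 26.0 v 28.0 | +2.0 |
| 20 | 30 | 20% v 10% | 22.0 v 21.0 | −1.0 |
| 20 | 7 | 15% v 15% | 18.05 v 18.05 | 0 |

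In the first row doubled mortality looks like a saving of 2.1 days. In the second, fewer deaths look like 1.4 days of harm. In the sixth, deaths come later than survivors' discharge and the sign reverses.

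- **Masking of a real effect.** If neostigmine shortens survivors' stay from 20 to 18 days, with deaths at day 7 and mortality 20% v 10%, the means are 0.80 × 20 + 0.20 × 7 = 17.4 and 0.90 × 18 + 0.10 × 7 = 16.9. A true saving of 2 days appears as 0.5 day.
- **Timing alone.** With 15% mortality in both arms but deaths at day 7 in one and day 10 in the other, the means differ by 0.15 × (10 − 7) = 0.45 day.

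**EN timing.** The number lost from an arm is 28 × m × (share of deaths that precede tolerated EN). The share is not in the documents.

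- Mortality 20% v 10%: 5.6 v 2.8 patients lost if all deaths come first, 2.8 v 1.4 if half do.
- Mortality 15% in both arms: 4.2 lost per arm, or 2.1 if half.

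**The case against.** **Silence.** The t-test sentence is generic and names none of these outcomes, and the handling of death is often left to an analysis plan that is not shown here. A reader might infer that the plan orders the deletion of patients who are never fed. It does not say so, and a ban on imputation is compatible with censoring or a worst-case rule. What remains is that the article fixes a test of means and excludes imputation. Followed as written, these leave such patients without a value, and handling death properly would mean departing from the stated test.

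**Resource use.** Stay and cost stand under health economics. Mean bed-days and mean cost over all patients, deaths included, are legitimate economic quantities. This stands, and cost is no part of the fault. The criticism applies to stay read as benefit, which the Objectives invite.

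**Size.** A reader might infer that the t-test would declare these artefacts significant. Take 28 per arm, S = 20 and D = 6, and no spread within survivors or within deaths. The standard error is √[(0.15 × 0.85 + 0.30 × 0.70) × 14² / 28] = 1.54 days for 15% v 30%, so t = 2.1 / 1.54 ≈ 1.37 (p about 0.18). For 15% v 5% it is √[(0.15 × 0.85 + 0.05 × 0.95) × 14² / 28] = 1.11 days, so t = 1.4 / 1.11 ≈ 1.26 (p about 0.21). Real spread would weaken both. The risk is a misleading estimate, or a real effect masked, more than a false positive.

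**Mortality.** A reader might take 15% as the death rate in the trial. It is a background figure for SAP, whereas Recruitment {15} and the Discussion have treatment starting before SAP can be confirmed at 48 h. Mortality among all randomized patients may be lower.

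**Safeguards.** Mortality is itself a secondary outcome and would be reported beside stay. The median, minimum and maximum are also reported. This helps a careful reader but does not repair the test. A reader might add that these outcomes are strongly skewed; the documents hold no data on that, and the point does not need it.

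**Conclusion.** The point holds in a limited form. As written, ICU stay, hospital stay and time to tolerated EN are compared by a t-test that has no place for death.

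- **Stay:** the difference in means is distorted if mortality or the timing of death differs between arms. In the illustrations with different mortality the shift is 1.0 to 2.1 days in either direction, all under assumed stays and assumed mortality by arm. With equal mortality and timing it is zero, although the mean still mixes survivors and deaths. The documents do not support saying that the stay comparison is biased in any event, or in one direction.
- **EN timing:** the comparison is restricted to a group selected after randomization as soon as any patient dies before tolerated EN. How many would do so cannot be read from the documents.
- **Cost:** the all-patient mean is sound as an economic measure, but not as evidence of clinical benefit.

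The wording should be changed before analysis. The matter concerns secondary outcomes only.

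**What to change.** State in the analysis section that three outcomes will be analysed in all randomized patients with death as a competing event: time from randomization to ICU discharge alive, to hospital discharge alive, and to tolerated EN. Alternatively, specify a rank test in which patients who die are ranked worst. Choose one and name it in advance, and say how a patient discharged alive without tolerated EN is handled.

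Keep mean bed-days and mean total cost over all randomized patients as resource-use measures. Report them beside mortality and do not read them as clinical benefit.

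The cost is small. The change needs only in-hospital dates and vital status that the trial already needs for its outcomes, and no extra patients, visits or follow-up. If the competing-event analysis is chosen, the team should confirm that the named software can run it. The one real downside is that the effect is no longer a simple difference in mean days. A measure such as days alive and out of hospital to a fixed day is less suitable here, because it needs vital status after discharge, which the trial does not collect.

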#### Participant timeline {13}

The participant timeline is presented in Table 2.

**Table 2 Tab2:**
[figure not shown]
Participant timeline

#### Sample size {14}

This is a randomized controlled trial. The bilateral significance level is 5% with an assurance of 90%. We estimate the standard deviation is 36 h, and the mean difference is 36 h. In the case of 1:1 ratio between intervention group and control group, a total of 44 patients will be needed (22 patients in each group). Considering a 20% drop-out rate, 56 patients will be recruited.

#### Recruitment {15}

A total of 56 patients will be recruited and participate in the study. Prior to recruitment, investigators will carefully study the medical history, laboratory test, and imaging test of each patient. If the patient meets the inclusion and exclusion criteria, researchers will fully consider the compliance of the patients and informed consent forms (ICFs) will be obtained before collecting any data or performing any intervention. After initial assessment and randomization, patients will receive intervention and 48 h after onset. If the patient still has evidence of organ failure, they will be diagnosed with SAP and will be formally enrolled in the study. The follow-up will be ended when the patients leave the hospital.

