**Methods:**

This trial is a randomized, placebo-controlled, double-blinded, mono-centric trial that will test the hypothesis that neostigmine can improve gastrointestinal motility in patients with severe acute pancreatitis. Up to 56 patients will be randomized in this study receiving 0.5 mg/1 ml of neostigmine methylsulfate injection twice per day or 1 ml of saline injection twice per day. Defection time (aim 1), mortality and organ failure (aim 2), borborygmus, starting of enteral nutrition and intra-abdominal pressure (aim 3), and length of ICU and hospital stay (aim 4) will be assessed.

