#### Intervention description {11a}

Participants will be randomized in a 1:1 ratio via computer-generated sequence randomization. The study will be blinded to participants. Neostigmine methylsulfate injection and the saline are prepared by pharmacists who are not involved in the study and are identical visually.

For experiment group, 0.5 mg/1 ml of neostigmine methylsulfate injection will be injected intramuscularly at the deltoideus triangularis twice a day right after the enrollment. For control group, 1 ml of 0.9% NS will be injected intramuscularly at the deltoideus triangularis twice a day.

Apart from intervention, other treatment of AP will be performed according to American Gastroenterological Association Institute Guideline [36].

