## Discussion

Gastrointestinal dysmotility is a common complication in AP patients, which can lead to delayed feeding and OFI. There is little evidence regarding the treatment of gastrointestinal dysmotility induced by AP. Neostigmine can increase gastrointestinal motility and has been used to treat gastrointestinal dysmotility after surgery. With this randomized, placebo-controlled trial, our aim is to investigate whether neostigmine is safe and efficacy for treating AP patients with gastrointestinal dysmotility. We would like to discuss some aspects and challenges of the study design in detail below.

First, the enrollment of patients: a diagnosis of SAP requires persist organ failure, which is defined as organ failure lasting over 48 h [4]. However, early intervention [38] plays an important role in treating AP patients, so we start intervention on patients within 24 h of onset, which will lead to brief intervention on moderate-severe acute pancreatitis patients.

Another point we would to address is the COVID-19 pandemic, which may lead to fewer patients, disturbing patient enrollment and even temporary interruption of the research. A delayed end of this study may occur.

In conclusion, a positive outcome of this trial will provide strong evidence as to the safety and efficacy of neostigmine in treating the gastrointestinal dysmotility for AP patients.

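### The protocol contradicts itself on whether randomised patients whose organ failure resolves by 48 h belong to the trial; leaving them out would select the primary population after randomisation

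*Protocol article*

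**What the plan says.** All places are in the protocol article.

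- **Eligibility criteria {10}, Table 1:** organ failure by the Marshall score is required at entry. Persistence is not.
- **Recruitment {15}:** after initial assessment and randomisation, patients receive the intervention. Once 48 h from onset have passed, this rule applies: "If the patient still has evidence of organ failure, they will be diagnosed with SAP and will be formally enrolled in the study". Follow-up ends when patients leave hospital.
- **Discussion:** early intervention is considered important, "so we start intervention on patients within 24 h of onset, which will lead to brief intervention on moderate-severe acute pancreatitis patients".
- **Intervention description {11a}:** injections are given "twice a day right after the enrollment".
- **Statistical methods {20a}:** the intention-to-treat set is defined as one from which nobody is excluded after randomisation.
- **Abstract, Methods:** "Up to 56 patients will be randomized in this study".
- **Sample size {14}:** "We estimate the standard deviation is 36 h, and the mean difference is 36 h", giving 22 per group. Then: "Considering a 20% drop-out rate, 56 patients will be recruited".
- **Objectives {7}:** reducing organ failure is among the effects hoped for from neostigmine.

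**The concern.** Entry to the trial seems to happen twice: at randomisation, and again at 48 h for those still in organ failure. The second entry comes after treatment has started and depends on organ failure, which the Objectives hope neostigmine will reduce. If only the second group is analysed, the arms being compared are no longer the arms that were randomised. Patients who improved early would be missing, possibly in different proportions by arm. Defecation time, mortality and new-onset organ failure would all be compared in that selected group.

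There is also a counting problem. The Abstract counts 56 as randomised, and the sample size section allows 20% for drop-out. Nothing says whether that allowance is meant to cover patients who do not meet the 48 h condition.

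**Working it through.** **1. The passages side by side.**

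| Question | One answer | Another answer |
|---|---|---|
| When is a patient enrolled? | Before the first injection ({11a}) | At 48 h, after treatment has begun ({15}) |
| Who is in the main analysis? | Everyone randomised ({20a}) | Suggested by {15} and the Discussion: those with persistent organ failure |
| What does 56 count? | Randomised patients (Abstract) | Recruited patients, after a 20% drop-out allowance ({14}); relation to formal enrolment not stated |
| Who is the population? | Organ failure at entry (Table 1) | Severe acute pancreatitis, i.e. persistent organ failure (Abstract, {7}, {15}) |

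No single reading satisfies every entry.

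**2. The plan's own sample size.** Inputs from {14}: two-sided 5%, 90% power, SD 36 h, difference 36 h, allocation 1:1.

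- Normal approximation: n per arm = 2 × (1.960 + 1.282)² × (36/36)² = 21.01, rounded up to 22, so 44 in total.
- Noncentral t with 22 per arm (42 degrees of freedom, noncentrality √(22/2) = 3.317): power 90.0%.
- Drop-out: 22/0.8 = 27.5, rounded up to 28 per arm, so 56.

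The stated figures reproduce. There is no arithmetic error.

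**3. Power if patients who resolve are left out.** Let q be the share of the 56 whose organ failure has resolved by 48 h. The document gives no value; 20 to 50% is an assumed range. With no other loss, n per arm = 28 × (1 − q), rounded down. If the 20% drop-out comes on top, the total is 56 × (1 − q) × 0.8. Power is noncentral t at the stated difference and SD.

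| q (assumed) | n per arm, no other loss | Power | Total with 20% drop-out on top | Power |
|---|---|---|---|---|
| 20% | 22 | 90% | 35.8 | 83% |
| 30% | 19 | 85% | 31.4 | 77% |
| 40% | 16 | 78% | 26.9 | 70% |
| 50% | 14 | 72% | 22.4 | 62% |

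If all 56 are analysed apart from a 20% loss, 56 × 0.8 = 44.8 remain and power is 90.5%, as planned.

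**4. Bias, as illustration only.** Take a standard normal severity score with correlation r to defecation time (SD 36 h), no treatment effect on defecation time, and organ failure that persists above a severity threshold. If a proportion p persists, mean severity among those persisting is φ(z)/p, where z is the threshold and φ the normal density. The spurious difference is 36 × r × (active mean − control mean).

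- Persistence 70% in both arms: difference 0.
- 70% control, 60% active: means 0.497 and 0.644; 36 × r × 0.147 = 1.6 to 3.7 h for r = 0.3 to 0.7.
- 70% control, 50% active: means 0.497 and 0.798; 36 × r × 0.301 = 3.3 to 7.6 h for r = 0.3 to 0.7.

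The persistence rates and correlations are assumptions; none is in the document. In this model the remaining treated patients are sicker, so the bias runs against neostigmine. Other mechanisms could reverse it.

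**The case against.** A reader might infer that the trial definitely drops patients who resolve, and so is biased and underpowered. The text does not go that far.

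- No sentence removes these patients from follow-up or analysis. The Discussion's remark concerns how long they are treated, not whether they are analysed. The intention-to-treat definition, its use for non-adherence in {20c} and the Abstract's count of randomised patients all point to keeping them. The flow chart and participant timeline, which might settle it, are not shown.
- The defined organ-failure outcome is new-onset failure, whereas the 48 h condition concerns failure already present. The Objectives are broad enough to include faster resolution, but the protocol does not claim it. That more patients would be lost from the active arm is an assumption.
- With no resolution rate given, it cannot be said outright that 90% power is not delivered. At 20% resolution with no other loss it still is.
- The word used in {11a} may simply mean initial entry, as distinct from formal enrolment.

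All this stands, and it limits the point to a contradiction with conditional consequences. It does not remove the contradiction. If everyone randomised is kept, formal enrolment at 48 h has no function and the population is not the severe acute pancreatitis population that the Abstract and Objectives name. Two teams following the protocol could analyse different patients.

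**Conclusion.** The contradiction is certain: formal enrolment at 48 h ({15}, with the Discussion) cannot be squared with no exclusion after randomisation ({20a}), and the Abstract and {11a} add further conflicting signals. The analysis status of randomised patients whose organ failure resolves is undefined.

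The consequences are conditional. If those patients are left out, as {15} and the Discussion suggest, the primary comparison loses the protection of randomisation. Neither the size nor the direction of bias can be derived from the document, and in the simple severity model it is zero when persistence is equal in both arms. Power would be 90 to 72% for an assumed 20 to 50% not formally enrolled and no other loss, and 83 to 62% if the 20% drop-out comes on top. If everyone randomised is analysed, the planned power stands at the plan's own assumptions. Because this decides who is in the primary analysis, it should be settled in the protocol.

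**What to change.** - Define enrolment as randomisation and remove formal enrolment at 48 h.
- State that every randomised patient is followed to discharge and included in the primary intention-to-treat analysis, whatever the 48 h status.
- Use persistent organ failure at 48 h only to define a labelled supportive analysis.
- Describe the population as acute pancreatitis with organ failure at randomisation.
- State that 56 counts randomised patients, what the 20% covers, and the resulting power.
- Reconcile {11a}, {15} and the Discussion on when treatment starts and for whom. Which rule applies is for the investigators; none is proposed here.

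The cost is protocol wording and a registry update. The downside is that the primary population will include some patients with transient organ failure, so the claim concerns early organ failure rather than confirmed severe acute pancreatitis. The effect may also be diluted: a difference of 30 h instead of 36 h, with SD 36 h and 22 per arm, gives 77% power. The 30 h is an example, not a figure from the document. The investigators should therefore check whether 36 h is still a reasonable assumption for the wider population before confirming that 56 is enough.
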